## SAFETY ASSESSMENTS

**See Section 7.1 above**

# DATA COLLECTION & MANAGEMENT

## Data Collection

The data will be collected by the research fellow or trial manager on paper with subsequent transcription to electronic form. Electronic storage will be in an encrypted form on a password protected device.

The medical notes will act as source data for past medical history & blood results. ECGs are printed and filed in medical notes.

## Data Management System

A data management system will be provided by TCTU using OpenClinica.  The study system will be based on the protocol and CRF for the study and individual requirements of the investigators.  Development and validation of the study database; and QC and extraction of data will be done according to TCTU procedures.  Extracts for analysis will be based on the dummy data tables provided by the study team.

# STATISTICS AND DATA ANALYSIS

## SAMPLE SIZE CALCULATION

**POWER CALCULATIONS**

In powering MRI studies of LVH regression, it is recommended that they are powered for a 10gm change in LV mass (= 4.8g/m^2^ change in LVMI). Grothues et al [[34](#_ENREF_34)] recommend this as this size of effect should reduce future CV events. We have powered this study based on two published studies where 12 months of treatment were given, as planned here. In Edwards et al [[35](#_ENREF_35)], there was a 10g reduction in LV mass with a standard deviation of 12g in CKD patients. Based on these values, we would need 32 patients per group to have 90% power at p<0.05 to detect this magnitude of change in LV mass. In the only MRI study which we have done involving one year of treatment, we saw an LV mass fall of 14 14 g, which would give us a very similar power calculation.[[36](#_ENREF_36)] (Unfortunately our allopurinol in mild CKD study only involved 9 months treatment and time is known to be crucial when a treatment is trying to regress LV mass : a larger effect is anticipated here with 12 months therapy). If we anticipate a 10% death or transplantation rate/year and a 10% dropout rate, then we will need a total of 76 patients to be recruited. Glasgow has 650 dialysis patients and Dundee 200, so that our planned recruitment should be achievable, especially since these patients are well aware of their poor prognosis and hence usually very willing to volunteer for potentially lifesaving research from which they may well personally benefit in the long term.

[figure not shown]

[figure not shown]

## PROPOSED ANALYSES

**Statistical Analysis**

Statistical analysis will be performed using SPSS (SPSS, Chicago, USA). Data will be expressed as mean ± SD unless stated otherwise. One-way ANOVA or χ^2^ test will be used to determine the significance of differences between both groups (normally distributed variable). Analysis of covariance will also be performed using the month 12 value as the dependent variable and the baseline value treated as a covariate, along with age, SBP, and DBP, to account for any differences in baseline measures of the primary and secondary outcomes. A *P* value <0.05 will be considered significant.

A detailed statistical analysis plan will be prepared during the trial.

## MISSING DATA

**This is an intention to treat study so all non compliers, withdrawn patients or missing data will be analysed by imputation. We will also do a completed cases only analysis.**

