**For the main Phase 2 ALTERED trial:**

Participants will be allowed to continue all their usual medication throughout.

After successful screening for eligibility and safety, participants will be randomised to either allopurinol or placebo in a double blind fashion. Participants and their bloods (U&Es, LFTs, FBC) will be monitored as per study schedule and medication stopped or reduced in dose if concerns arise. If study drug dose is reduced, they will remain in the study. If study drug needs to be stopped, they will remain in the study in order to do an “intention to treat” analysis.

Double blind medication (allopurinol or placebo) will be prepared, packaged and labelled by Tayside Pharmaceuticals. The medication will come labelled as “Participant 1”, “Participant 2”, etc. and will be distributed to the participant by the research fellow according to their sequence number. Randomisation will be carried out by Tayside Pharmaceuticals using block randomisation. They will use a validated randomisation program and will securely backup both the randomisation seed and the randomisation allocation. Two copies of the allocation will be supplied with the IMP & placebo tablets to the Clinical Trials Pharmacy, Ninewells, and to the Clinical Trial Pharmacy at Western Infirmary, Glasgow who operate a 24 hour emergency unblinding facility.

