### Treatment Allocation

Participants will be given blinded medication. At the randomisation visit they will be dosed with either allopurinol 100mg or matched placebo.

They will then be asked to take one tablet after each dialysis session for two weeks (+/-2 days).

Thereafter the medication will be increased weekly (after 3 dialysis sessions) as tolerated (+/- 2 days) to the dose decided in the pilot study – ie one week at 200mg, one week at 250mg, one week at 300mg and upto 350mg, or placebo as determined by pilot data.

Compliance will be checked and documented using tablet counts at each visit. If non-compliant, they will be encouraged to become compliant. If they persist as non compliant, (<70% compliant) they will stay in the study, but not on study medication, in order to do an “intention to treat” analysis.

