### Withdrawal procedures

Side effects are likely to be minor and expected and it will therefore be a participant choice as to whether they withdraw or not from a study. Rash is the main side effect and withdrawal will occur if it is marked as persistent. Participants who withdraw will be replaced if possible within the study timeframe. Contact (by telephone) will be maintained by the research fellow/trial manager/research nurse with those who withdraw to ensure resolution of adverse event(s). The reasons for withdrawal will be noted in the participant’s CRF and casenotes. If withdrawal is due to an AE it will be logged as such on the Adverse Event Log.

Participants are free to withdraw from the study at any time. The reasons, if known, will be recorded in the medical casenotes and CRF.

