## DOSING REGIME

Participants will be given blinded medication. At the randomisation visit they will be dosed with either allopurinol 100mg or matched placebo.

They will then be asked to take one tablet after each dialysis session for two weeks (+/-2 days).

Thereafter the medication will be increased weekly as tolerated (+/- 2 days) to the dose decided in the phase 1 dose escalation study – ie one week at 200mg, one week at 250mg, one week at 300mg and upto 350mg, or placebo as determined by pilot data.

Compliance will be checked and documented using tablet counts at each visit. If non compliant, they will be encouraged to become compliant. If they persist as non compliant (<80% compliance), they will stay in the study, but not on study medication, in order to do an “intention to treat” analysis.

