### Prohibited Medications

6-mercaptopurine or azathioprine: concurrent prescription of either of these drugs would not be allowed due to the known interaction of these drugs with allopurinol. Any participants already on these drugs would be excluded at screening. If they needed to start on treatment with either of these whilst receiving study medication then they would be withdrawn from study.

Warfarin: due to the possible influence of allopurinol on warfarin levels (requiring increased frequency of monitoring) any participants already on a stable dose of this drug would be excluded at screening. If they needed to start on treatment with warfarin whilst receiving study medication then this would however still be possible (as any patient newly commenced on warfarin has frequent monitoring of their INR).

Theophylline: due to the possible influence of allopurinol on theophylline levels any participants already on this drug would be excluded at screening. If they needed to start on treatment with theophylline whilst receiving study medication then they would be withdrawn from study.

Ampicillin/amoxicillin: not prohibited, but an increase in frequency of skin rash has been reported among s receiving ampicillin or amoxicillin concurrently with allopurinol compared to patients who are not receiving both drugs. The cause of the reported association has not been established. However, in participants receiving allopurinol an alternative to ampicillin or amoxicillin will be used where available.

The GP information letter and PIS will contain information on all the above points.

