**Screening**

All dialysis patients aged 18-80 screened for eligibility at dialysis clinics in NHS Tayside & NHS GGC (N=250,Tayside, N= 650 NHS GGC)

Analysed (n=34)
♦ Excluded from analysis (give reasons)(n= 4)

Analysed (n=34)
♦ Excluded from analysis (give reasons)(n= 4 )

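### Section 9.3, read as written, imputes over the measured month-12 outcomes of non-compliers whom the protocol keeps in the study for an intention-to-treat analysis

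*Protocol*

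**What the plan says.** **Analysis rule (9.3).** "This is an intention to treat study so all non compliers, withdrawn patients or missing data will be analysed by imputation". The section adds: "We will also do a completed cases only analysis".

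**Retention of patients off drug.**
- 5.5.1, drug stopped: "If study drug needs to be stopped, they will remain in the study in order to do an" ITT analysis.
- 5.5.2, persistent non-compliance, threshold 70%: "they will stay in the study, but not on study medication, in order to do an" ITT analysis.
- 6.3, the same rule with another threshold: "If they persist as non compliant (<80% compliance), they will stay in the study, but not on study medication".
- 6.4, drug stopped for abnormal bloods: the patient stays in for the full study duration.
- 6.5: compliance under 70% leads to withdrawal from treatment.

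**Withdrawal from the study (6.7.2).** For theophylline: "If they needed to start on treatment with theophylline whilst receiving study medication then they would be withdrawn from study". Azathioprine and 6-mercaptopurine have an equivalent sentence.

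**Replacement (5.5.4).** "Participants who withdraw will be replaced if possible within the study timeframe".

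**Projected flow chart (Appendix 4).** Each arm shows 38 allocated, 4 lost to follow-up, 34 analysed, and a box reading "Excluded from analysis (give reasons)(n= 4".

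**Primary outcome.** Change in LVMI by MRI (2.2.1). The MRI is scheduled at screening and at month 12 (7.1, Appendix 3).

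**The concern.** An ITT analysis uses the outcome of each randomised patient in the allocated arm, whether or not the drug was taken. The protocol keeps non-compliers under follow-up for that purpose, so most should have a month-12 MRI. Section 9.3 then names them, beside missing data and not within it, as a group to be imputed. If the analyst follows that sentence, observed primary outcomes are set aside for modelled ones, and the result may estimate something other than the effect of assignment. This governs the primary comparison of a 76-patient trial.

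Two other inconsistencies feed the same sentence. The group to be imputed has two definitions. And section 6.7.2 takes some patients out of the study altogether, where 5.5.1 and 6.4 say that a patient who stops drug remains in it. That decides whether an outcome is measured at all.

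**Working it through.** **1. The rules side by side**

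| Patient | Study status | Month-12 MRI due? | Handling under 9.3 as written |
|---|---|---|---|
| Non-complier | Stays in, off drug (5.5.2, 6.3) | Yes | Imputed |
| Drug stopped | Stays in (5.5.1, 6.4) | Yes | Imputed if counted as a non-complier or as withdrawn; the text does not say |
| Starts azathioprine, 6-mercaptopurine or theophylline | Withdrawn from study (6.7.2) | Not stated; conflicts with 5.5.1 and 6.4 | Imputed |
| Lost to follow-up | Out | Not obtained | Imputed |

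Only in the last row is imputation clearly needed. In the first row it replaces a measurement that the protocol arranged to collect.

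**2. Who is a non-complier**

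A patient with 75% compliance is a non-complier under 6.3 (75 < 80) but not under 5.5.2 or 6.5 (75 > 70). Under 9.3 the same patient's MRI would be imputed by one definition and used by the other.

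**3. The planned effect**

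Section 9.1 uses a 10 g difference in LV mass, SD 12 g, p<0.05 (two-sided assumed) and 90% power, and states 32 per group. A two-sample t-test gives 32 per group (power 90.7%; 31 per group gives 89.8%), so the figure reproduces. Section 9.1 equates 10 g with 4.8 g/m² in LVMI.

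**4. Illustration of possible bias**

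The 10 g comes from 9.1. The rest is assumed: a fraction p of the active arm are non-compliers, they gain nothing, and placebo patients do not change.

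- Effect of assignment: 10 × (1 − p) + 0 × p = 10(1 − p).
- Non-compliers imputed from compliers: 10 × (1 − p) + 10 × p = 10 g.
- Overstatement: 10p g, or a ratio of 1/(1 − p).

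| p | ITT effect | Reported | Overstatement |
|---|---|---|---|
| 0.10 | 9 g (4.8 × 0.9 = 4.32 g/m²) | 10 g | 1 g, 11% |
| 0.20 | 8 g (4.8 × 0.8 = 3.84 g/m²) | 10 g | 2 g, 25% |

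**5. The same case under another imputation model**

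The only earlier MRI is at screening. Carrying it forward gives each non-complier zero change, so the estimate is 10(1 − p) = 9 or 8 g, equal to the ITT effect. Under these assumptions the bias disappears. Its existence and direction therefore depend on a model that the protocol does not state.

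**6. The flow chart**

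38 − 4 lost = 34, and 38 × 0.9 = 34.2. The 4 shown as excluded match the 4 lost to follow-up; they are not a second loss.

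**The case against.** The strongest defence is that the sentence stands under a heading on missing data and opens by declaring ITT. Read with 5.5.1, 5.5.2 and 6.3, it may mean only that everyone is included and gaps are filled. The imputation model is ordinary SAP content, and 9.2 promises a SAP. This is a plausible account of the intention, and the model's absence is no fault. But the protocol itself fixes which patients are imputed. If only gaps were meant, naming non-compliers beside missing data would be redundant.

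A reader might infer three stronger points, which the documents do not support.

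- *Appendix 4 excludes 4 patients per arm from the ITT analysis.* The appendix gives projected numbers in a template, and the 4 are the projected losses. The 34 fits the completed-case analysis that 9.3 also plans. The box lacks a label; it is not a rule.
- *Replacing withdrawn patients breaks the randomised comparison.* Section 5.5.4 does not remove the withdrawn patient, and 9.3 keeps withdrawn patients in the analysis. Medication is handed out blinded by sequence number (5.5.1), so an added patient would presumably take the next number.
- *Discarding these MRIs costs power.* With 20% attrition (10% + 10% in 9.1), 38 × 0.8 = 30.4 per arm are observed. At 10 g and SD 12 g, power is 89.2%; it is 85.7% or 81.2% if a further 10% or 20% are dropped (27.4 or 24.3 per arm). But those figures hold the effect at 10 g. The recommended analysis targets 9-8 g under the same assumptions, with 82-72% power at 30.4 per arm. The comparison is not like for like and shows no loss.

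The conflict over study withdrawal in 6.7.2 is real but narrow: it covers three newly started drugs, and no frequency is given.

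**Conclusion.** The concern holds for section 9.3. As worded, it contradicts the declared ITT principle and the stated reason for retaining non-compliers, because it sends patients with measured primary outcomes to imputation. The accurate statement is that the comparison could be biased, not that it would be. The 1-2 g (11-25%) overstatement is an illustration that needs 10-20% non-compliance, no benefit in non-compliers and imputation from compliers. None of these is in the protocol, and carrying the screening value forward removes the bias under otherwise equal assumptions.

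Two inconsistencies stand with it: the 70% and 80% compliance thresholds, and the conflict of 6.7.2 with 5.5.1 and 6.4 on remaining in the study. Replacement and the Appendix 4 numbers need clearer wording but do not in themselves contradict ITT.

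**What to change.** 1. **Section 9.3.** State that every randomised patient is analysed in the allocated arm, that the observed month-12 value is used whatever the compliance or treatment status, and that only truly missing values are imputed. Keep the completed-case analysis as the additional one.
2. **Sections 5.5.2, 6.3 and 6.5.** Reconcile the compliance thresholds so that the term has one meaning. Which figure applies is for the investigators.
3. **Section 6.7.2 against 5.5.1 and 6.4.** Reconcile whether outcome follow-up continues once study drug stops. No view is taken on the clinical rule.
4. **Minor wording.** In 5.5.4, say that a withdrawn patient who is replaced stays in the ITT analysis. In Appendix 4, label the 34 per arm as the projected completed-case set.

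The cost is protocol wording. The month-12 MRI is already scheduled for patients who stay in the study off drug. If item 3 is resolved in favour of continued follow-up, the few patients under 6.7.2 would also have the MRI already planned for them.

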# ADVERSE EVENTS

Adverse event reporting will be carried out in accordance with TASC SOP 11: Identifying, Recording and Reporting Adverse Events for Clinical Trials of Investigational medicinal Products. The CI (or delegate) is responsible for the detection and documentation (and reporting, where required) of adverse events

The IMP (investigational medicinal product) reference document to be used when assessing causality will be the SmPC.

All reported adverse events (AEs) will be recorded in detail on an adverse event CRF page For all AEs, the Investigator will initiate the appropriate treatment according to their medical judgment.

## DEFINITIONS

An **adverse event** (AE) is any untoward medical event affecting a clinical trial participant. Each initial AE will be considered for severity, causality or expectedness and may be reclassified as a serious event or reaction based on prevailing circumstances.

An **adverse reaction** (AR) is where it is suspected that an AE has been caused by a reaction to a trial drug

A **serious adverse event** (SAE), **serious adverse reaction** (SAR) or **suspected unexpected serious adverse reaction** (SUSAR) is any AE, AR or UAR that at any dose:

- results in death
- is life threatening
- requires hospitalisation or prolongation of existing hospitalisation
- results in persistent or significant disability or incapacity
- is a congenital anomaly or birth defect
- Or is otherwise considered serious

**Note:** Hospitalisations for treatment planned prior to randomisation and hospitalisation for elective treatment of a pre-existing condition **will not** be considered as an SAE. Additionally hospitalisations related to shunt problems, infections, and cardiovascular events such as heart failure or acute coronary syndrome will not be considered as SAEs though will be noted as adverse events and recorded. Any adverse events occurring during such hospitalisation must though be recorded.

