Having shown clearly that allopurinol can regress LVH in mild (stage 3) CKD patients, we feel that the next stage is to see if this beneficial effect occurs also in patients with severe CKD i.e. patients with ESRD. After all, it looks from large clinical trials that lowering cholesterol is beneficial in mild CKD but not in the dialysis population, which shows that separate studies are always necessary in these two populations and that one cannot extrapolate from one population to the other.[[26](#_ENREF_26), [27](#_ENREF_27)] This result with cholesterol lowering is probably because coronary atherosclerosis is the main culprit in mild CKD whereas the main culprits in ESRD are LVH driven events such as arrhythmias and heart failure. This is further justification for using LVH regression as the main endpoint when seeking new treatments to reduce the high incidence of CV events/mortality in ESRD.

Our proposed study in ESRD would not only provide “proof of concept” evidence enabling this new therapy to move forward to be tested in an endpoint trial in ESRD but it would also act as important confirmation of the whole concept that allopurinol can regress LVH in CKD. After all no one is going to fund an endpoint mega trial in ESRD without this (necessary) piece of evidence in this exact cohort of patients. In doing this trial in ESRD we shall see if allopurinol improves another important surrogate i.e. endothelial dysfunction. Since allopurinol has always improved endothelial function in all previous patient studies, it seems likely that it will do so again in ESRD and this study will be an opportunity to acquire these key data which will help make the case for a mega trial in ESRD. It will also produce pilot data that allopurinol is likely to be tolerated and safe in ESRD which will also be essential, as a preliminary to an ESRD mega trial. What will assist also in eventually making the case for this future mega trial is a small (n=113) study where allopurinol reduced CV events by 71% although admittedly this was in patients with mild CKD.[[22](#_ENREF_22)] Since CV events are commoner in ESRD than in mild CKD, an endpoint trial in ESRD would also be less expensive. Indeed, it is traditional to do such mega trials first in severe disease and only later in milder disease, because CV event rates are higher in severe disease.

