### Secondary Objectives

- To decide on optimum dosing regime of allopurinol in ESRD from pilot study.
- To assess effect of allopurinol on endothelial function as measured by FMD and PWA.
- To assess safety of allopurinol in ESRD.

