## RECORDING AEs AND SAEs

Depending on severity, when an AE occurs, the CI or delegate will review all documentation (e.g. hospital notes, laboratory and diagnostic reports) related to the event. The CI or delegate will then ensure that all relevant information is recorded on the adverse event CRF page. If the event is an SAE, SAR or SUSAR, an SAE form must also be completed and sent to the Sponsor Pharmaco-vigilance Section.

Information to be collected will include dose, type of event, onset date, Investigator assessment of severity and causality, date of resolution as well as treatment required, investigations needed and outcome.

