## DATA MONITORING COMMITTEE

This is not felt necessary as this is a relatively small study involving an already marketed drug. The research group have also previously done many similar studies with allopurinol with no major problems.

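### Section 10.1 removes serious status from infection, cardiovascular and shunt admissions regardless of causality, so a non-fatal suspected reaction among them need not be reported as serious

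*Protocol*

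**What the plan says.** Protocol Section 10.1 gives one list of seriousness criteria for SAEs, SARs and SUSARs together. One item on it is an event that "requires hospitalisation or prolongation of existing hospitalisation". A Note below the list first sets aside admissions planned before randomisation and elective admissions for pre-existing conditions, which is not at issue here. It then goes further: "Additionally hospitalisations related to shunt problems, infections, and cardiovascular events such as heart failure or acute coronary syndrome will not be considered as SAEs". These admissions are kept as ordinary adverse events: "though will be noted as adverse events and recorded". Earlier in the same section, any adverse event "may be reclassified as a serious event or reaction based on prevailing circumstances".

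Section 10.3 ties the sponsor form to the classification: "If the event is an SAE, SAR or SUSAR, an SAE form must also be completed". Safety is a secondary objective in Section 2.1.2: "To assess safety of allopurinol in ESRD". Section 12.4 dispenses with a data monitoring committee: "This is not felt necessary as this is a relatively small study involving an already marketed drug".

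**The concern.** The Note changes what counts as serious; it does not merely relax how fast something is reported. It applies to three broad classes of admission and says nothing about whether the investigator suspects the study drug. A cardiovascular or infective admission judged probably drug-related is treated like one judged unrelated.

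The stakes are twofold. For participants, a non-fatal suspected reaction in these classes may not reach sponsor pharmacovigilance as a serious reaction, and so may not be assessed for SUSAR reporting. For the analysis, SAE and SAR counts will be too low in categories that matter for the next step. Section 1.1 says of this trial that "It will also produce pilot data that allopurinol is likely to be tolerated and safe in ESRD", as a preliminary to a large trial of cardiovascular events. Section 10.2 also states that reactions to allopurinol are more frequent when there is renal disorder, which describes every participant.

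**Working it through.** No figure in the plan is involved, so the check follows one event through Section 10. Take an admission for infection that is not fatal, life-threatening or disabling, is not otherwise considered serious, and is judged probably related to study drug.

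1. **Section 10.1, criteria.** The admission meets the hospitalisation criterion, so the event would be serious.
2. **Section 10.1, Note.** The admission is for infection, so it is declared not to be an SAE. No causality condition stops this. Steps 1 and 2 conflict, and the Note is the more specific and more firmly worded rule.
3. **Section 10.4.1.** Seriousness is to be assessed by the definition in Section 10.1. This leads back to the Note and offers no independent test.
4. **Section 10.4.2.** A related AE becomes an AR, and a related SAE becomes a SAR. Since the event is not an SAE, it becomes an AR. Causality alone does not confer seriousness.
5. **Section 10.3.** The SAE form is required for an SAE, SAR or SUSAR. The event is none of these, so no form is mandatory.
6. **Section 10.5.** The 24-hour report applies to SAEs. It is not triggered.
7. **Section 10.6.** The 7-day and 15-day regulatory reports apply to SUSARs, which must be serious. They are not triggered.

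The event ends as a non-serious adverse reaction on the adverse event page of the CRF.

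Next, the provisions that might bring it back:

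- **Reclassification in Section 10.1.** This is permissive, is not linked to a causality judgement, and stands against a flat exclusion a few lines later.
- **AE recording in Section 10.3.** The listed items include severity, causality, treatment and outcome. They do not name hospitalisation, and Section 10.4.3 warns that severity is not seriousness. The event is kept, but the list does not by itself ensure that it can be picked out as an admission.
- **Section 10.7.** One trigger is a change in the rate or nature of expected SARs, and events barred from SAR status do not enter that count. Another covers new trial-related events likely to affect participants' safety. It could apply, but it rests on judgement about a pattern and is not a rule for the single case.

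Finally, what the Note leaves alone. It speaks of hospitalisations only. Death, threat to life, persistent or significant disability and the residual category of otherwise serious events are separate criteria in Section 10.1, and an event meeting one of them remains an SAE. The gap is therefore confined to events whose only seriousness criterion is the admission.

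**The case against.** The strongest reply is that the exemption is deliberate and of a familiar kind. Dialysis patients are often ill for reasons unrelated to the drug, and sending every such admission through 24-hour reporting would create noise. The events are recorded with severity and causality, so an analyst could tabulate them by arm. Dialysis staff see participants three times a week and alert the investigators (Section 10.2). Section 10 also places reporting under a sponsor SOP that is not shown and might limit the exemption. The Note uses the term SAE and does not name SAR or SUSAR.

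Much of this stands. Exempting expected, unrelated admissions from expedited reporting is a reasonable choice, and the data are not discarded. It does not answer the narrower point. The reporting burden justifies relaxing the timing for unrelated events; it does not justify removing serious status from suspected reactions. SAR and SUSAR share the SAE criteria in Section 10.1, and under Section 10.4.2 a SAR arises from a related SAE, so leaving them unnamed in the Note does not protect them. An unseen SOP cannot be assumed to override the protocol's explicit definition.

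A reader might also infer more than the text supports:

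- **That deaths are lost.** Section 1.1 gives annual mortality approaching 10%, almost half of it cardiovascular. For 76 patients that is 76 × 0.10 = 7.6 deaths, of which about 7.6 × 0.5 = 3.8 would be cardiovascular. None of these is lost, because death is a separate criterion.
- **That severe cases are exempt too.** Life-threatening and disabling events are not.
- **That the safety objective loses its main serious events, or that the sponsor never sees them.** The admissions remain in the AE data, no admission rate shows that they are the main serious events, and discretionary routes to the sponsor exist. What is missing is a mandatory one.

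**Conclusion.** The point holds in a limited form. On its wording, the Section 10.1 Note conflicts with the hospitalisation criterion in the same section. It leaves suspected reactions that are serious only through a shunt-related, infective or cardiovascular admission outside mandatory SAE, SAR and SUSAR handling. The consequences are understated SAE and SAR counts and possibly missed expedited reports of non-fatal suspected reactions.

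The number of events affected cannot be estimated, because the protocol gives no admission rate for any of the three classes and no expected proportion judged related. The conclusion rests on a literal reading of Section 10 and on the unseen SOP not closing the gap. The absence of a data monitoring committee is a separate choice. It adds some weight here because the steering committee is the project management group itself (Sections 12.1 and 12.3), which makes sponsor pharmacovigilance an important check from outside the trial team.

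This should be corrected. It is a stated rule that gives a wrong result for an identifiable class of events, and the change is small.

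**What to change.** Reconcile the Note with the seriousness criteria in Section 10.1 and the causality rule in Section 10.4.2:

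- Keep hospitalisations for shunt problems, infections and cardiovascular events classified as serious.
- Require a causality assessment for each one.
- Reword the Note as an exemption from 24-hour reporting only. It should apply when the admission is judged unrelated to study drug and the event meets no other seriousness criterion. Any suspected reaction then follows the usual SAR and SUSAR route.
- Include all these admissions, exempted or not, in the serious-event tabulation by arm.
- Check the new wording against the sponsor SOP cited at the start of Section 10.

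The cost is a wording change in Section 10.1 and some additional SAE forms. Keeping the reporting exemption for unrelated admissions limits the extra urgent work.
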